       2. Measurement items: Aspatate transaminase(AST), Alanine transaminase(ALT), Gamma glutamyl peptidase(GGT), Total Bilirubin, BUN, Creatinine, Total cholesterol, Glucose
       3. Measurement method

- Refrain from caffeine, alcohol, and tobacco consumption the day before the test
- 8-hour fasting is required before the test; water allowed
- Test takes 10 minutes

1. [**3D Blood pressure and pulse wave test]**: **3d pulse wave imaging device (3D MAC, ㈜ Daeyomedi Co., Ltd., South Korea)**: 10 minutes ( See [Attachment 1])
   - - 1. Pulse strength value and stage (Unit:gf)
       2. Pulse depth value and stage (Unit:gf/cm^2)
       3. Pulse velocity value and stage (Unit:beats)
       4. Pulse shape value and stage (Unit:step)
       5. Radial artery augmentation index(R-AI) (Unit:%)
       6. SBP (Unit:mmHg)
       7. DBP (Unit:mmHg)
       8. Pulse pressure (PP) (Unit:mmHg)
       9. Pulse rate (PR) (Unit:beats/min)
       10. Cardiac output (1 beat) SV (Unit:mL/beat)
       11. Cardiac output (1 minute) CO (Unit:L/min)
       12. Systemic vascular resistance index(SVRI) (Unit:dyn*s/cm^5/m^2)
2. European Quality of Life Five Dimension Five Level Scale (EQ-5D-5L) questionnaire: 5 minutes ( see [Attachment2] )
3. Other

Adverse events and concomitant treatments are monitored per patient’s report and questions at every visit

1. Outcome measurement criteria and method
2. Primary outcome

This study is an exploratory observational study aiming to explore the safety and BP-lowering effetcs of modified SMS prepared and prescribed by Kyung Hee Bi, Che, Dam Korean Medicine Clinic for patients with HTN by comparing SBP before and after treatment.

1. [Changes in MSSBP] use Omron Healthcare HEM-9000AI
   Amount of change in MSSBP at end of treatment (visit 3) compared to the baseline (visit 1)
   - - 1. Null hypothesis (H0): There is no difference in MSSBP between the baseline (Visit 1) and end of treatment (visit 3).
       2. Alternative hypothesis (HA): There is a difference in MSSBP between the baseline (Visit 1) and end of treatment (visit 3).
2. Secondary outcome
3. Amount of change of MSSBP at visit 2 compared to the baseline (visit 1)
4. Amount of change of MSSBP at visits 2 and 3 compared to the baseline (visit 1)
5. Percentage of participants with normalized BP: percentage of patients who achieved normal BP compared to MSSBP/MSDBP measured at each time point (percentage of patients who had a BP of less than 140/90 mmHg at end of treatment)

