6. BP response rate at end of treatment (visit 3) compared to the baseline (visit 1) (percentage of patients who had MSSBP drop by 20 mmHg or more or MSDBP drop by 10 mmHg or more)
7. Amount of change in individual parameters on 3D pulse wave imaging at visits 2 and 3 compared to the baseline (visit 1)
8. Amount of change in EQ-5D-5L score at visits 2 and 3 compared to the baseline (visit 1)
9. Outcome evaluation criteria

This study is a prospective study conducted to present data for subsequent studies on modified SMS; the purpose is not to determine the clinical efficacy of the drug, but rather, to explore and collect preliminary data.

However, for the statistical analysis in this study, we will present the degree of improvement in the continuous variables using descriptive statistics.

Efficacy is determined based on the improvement of MSSBP, 3D pulse wave imaging parameters, and Eq-5D-5L score at visits 2 and 3 compared to the baseline, and the percentage of patients who have achieved such improvements is presented. However, because the study is an exploratory study without a control group, there are limitations in determining efficacy.

As this study observes effects during a routine treatment protocol, we will collect the following data that may potentially influence BP and control for them in the analysis.

* Collection of information about the use of antihypertensive drugs.
* If the patient is using antihypertensive medication, they are informed to notify the investigator upon changes in the dose and dosage of the drug.
* Patients are informed to maintain their normal lifestyle, including exercise and diet

ANCOVA is performed with sociodemographic variables that may affect HTN, namely sex, age, BMI, duration of HTN, comorbidity, BP at initial visit, use of antihypertensive medication, and types of drugs, controlled for as covariates.

1. Anticipated AEs, precautions, and measures to address them
2. Additional AEs anticipated as a result of participation in observational study

In this observational study, the same process used in the standard treatment protocol is used, which involves taking modified SMS, performing tests and questionnaires, and documenting them in the CRF. Thus, there are no additional tests or interventions performed other than those included in the standard treatment process; for this reason, there are no other anticipated AEs in addition to the AEs that may occur during the standard treatment process.

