This study is an observational study collecting clinical data and observing the clinical course of patients taking modified SMS, and there are no interventions other than the herbal medicine regimen or any additional tests required for study participation. If an AE occurs nonetheless, the herbal medicine regimen will be discontinued, and the patient will be observed and treated as necessary until the event is resolved per the general treatment protocol at Kyung Hee Bi, Che, Dam Korean Medicine Clinic.

Measures taken for abnormal blood test results: liver function test including aspartate transaminase (AST), Alanine transaminase (ALT), Gamma glutamyl peptidase (GGT), and total bilirubin, as well as BUN, creatinine, total cholesterol, and glucose are measured on visits 1, 2, and 3. Per the general treatment protocol at Kyung Hee Bi, Che, Dam Korean Medicine Clinic, additional use of herbal medicine regimen is suspended if the levels rise more than twofold, along with the standard medical measures (including tests) for f/u.

Given the minimal anticipated side effects, the study is not expected to have substantial safety issues. As a rule, safety parameters are monitored, and any incidence of AEs will be notified to the PI and co-investigators. Upon onset of an AE, appropriate medical measures will be taken until recovery.

1. Evaluation of safety parameters

Safety evaluation will be performed for all AEs that occur during the study period. The rate of AE, rate of AE that led to discontinuation, and rate of SAE are reported. For the rate of AEs, all AEs and AEs associated with Korean medical care and intervention will be presented.

VS or blood test results will be reviewed comprehensively to determine normal/abnormal results, and items deemed clinically significant by the clinician can be analyzed statistically as necessary.

1. Data analysis and statistical methods

Efficacy evaluation will be performed using the FAS. Safety data will be analyzed with the safety set. All analyses will be conducted using the SAS Version 9.4 (SAS Inc, Cary, NC) software, and all statistical tests not defined separately will be performed as a two-tailed test and 5% significance level. Any missing values in the FAS will be imputed using the Last Observation Carried Forward (LOCF) method for the efficacy evaluation. All other data will be analyzed as is.

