Full Analysis Set(FAS): Per the Intention-to-Treat (ITT) principle, FAS includes participants who have received the herbal medicine preparation at least once and have had at least one measurement of the primary outcome measure

Safety Set (SS): Includes participants who have received the herbal medicine preparation at least once and have had at least one safety-related f/u

For demographic and baseline data, categorical data will be presented as n (%), and continuous data will be presented as mean±SD.

For efficacy parameters, continuous variables will be analyzed with paired t-test or Wilcoxon signed rank test, and categorical variables will be analyzed using the McNemar test or McNemar Exact test depending on their normality.

For safety parameters, adverse drug reactions (ADRs), SAEs, and serious ADRs will be presented as n (%), and differences across time points will be analyzed using the McNemar test or McNemar Exact test.

ANCOVA model will be used for analysis with sociodemographic factors that may affect HTN, such as sex, age, and use of antihypertensive drugs, included as covariates.

1. Withdrawal of consent and discontinuation
2. Discontinuation criteria

Participants may be discontinued from the trial in the following instances:

- Participants or their legal representatives requests discontinuation or participant withdraws consent due to unsatisfactory treatment effects during the study period
- Violation of inclusion criteria or meeting exclusion criteria
- Failure to take the modified SMS even once during the observational study period, despite giving consent and meeting eligibility criteria
- Occurrence of SAE related to the herbal medicine or AE making continuation in the study difficult
- Change of prescription during study
- Participant’s violation of study plan
- Lost to f/u during study period
- Other reasons due to which continuation of study is deemed inappropriate by the investigator

1. Study termination criteria

Upon occurrence of SAE suspected to be caused by the investigational drug, the PI notifies the joint IRB within 24 hours and terminate the study.

The clinical trial may be terminated prematurely in the following cases:

- Harmfulness of investigational product is discovered
- Moderate or severe AE deemed to have a relationship with the clinical trial occurred in more than 25% of the entire study population
- Study poses threat to the safety and well-being of study participants

1. Withdrawal of consent

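### McNemar's test does not fit the BP response rate: response has no visit 1 value, so the test only asks whether the rate differs from 0%

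*Protocol*

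**What the plan says.** Protocol section 16 (Data analysis and statistical methods) sorts the efficacy variables into two kinds. For one, "continuous variables will be analyzed with paired t-test or Wilcoxon signed rank test"; for the other, "categorical variables will be analyzed using the McNemar test or McNemar Exact test", with normality given as the criterion for the choice. Tests not defined separately are to be "performed as a two-tailed test and 5% significance level". No other test for a categorical efficacy variable is named, and the BP response rate is not exempted.

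Section 13.B (Secondary outcome) lists two yes/no blood pressure outcomes:

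- Response at visit 3 relative to visit 1, defined as the "percentage of patients who had MSSBP drop by 20 mmHg or more or MSDBP drop by 10 mmHg or more".
- Normalised BP, defined as the "percentage of patients who had a BP of less than 140/90 mmHg at end of treatment".

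Section 13.C adds that the study is not meant to establish clinical efficacy, that improvement will be described, and that the percentage of patients who improve will be presented.

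**The concern.** McNemar's test compares a yes/no state recorded twice in the same patient. Normalised BP is such a state, because a patient can be above or below 140/90 mmHg at either visit. Response is not. It is a dichotomised change that exists once, at visit 3, and every patient is a non-responder at visit 1 by definition. The before-after table therefore has a structural zero, and the null hypothesis becomes a response rate of 0%.

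That null is not worth testing. Blood pressure varies between visits, so some patients will cross a 20/10 mmHg threshold with no treatment effect. Entry also requires a raised systolic pressure, so regression to the mean would add more. A significant result would show only that some patients' pressures fell, yet it could be read as evidence that the treatment works.

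The rule for choosing between the two versions of the test makes this worse. It is tied to normality, which has no meaning for a categorical variable, and the two versions need different numbers of responders to reach 5%.

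**Working it through.** **The plan's own figure.** The only calculated figure is the sample size: 20 patients with data after 33% dropout. 20 / (1 − 0.33) = 29.9, rounded up to 30. This reproduces. No response rate, SD of change or power is stated.

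**The table under the definition.** Let k be the number of responders at visit 3.

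- Non-responder at visit 1, responder at visit 3: b = k.
- Responder at visit 1, non-responder at visit 3: c = 0 always.

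**The p-value.**

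- Exact, two-sided: p = 2 × 0.5^k.
- Uncorrected chi-square: (b − c)² / (b + c) = k, on 1 df.
- Continuity-corrected chi-square: (k − 1)² / k, on 1 df.

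| Responders k | Exact p | Uncorrected p | Corrected p |
| --- | --- | --- | --- |
| 3 | 0.25 | 0.083 | 0.248 |
| 4 | 0.125 | 0.046 | 0.134 |
| 5 | 0.063 | 0.025 | 0.074 |
| 6 | 0.031 | 0.014 | 0.041 |

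The number of non-responders enters none of these formulas. Six responders give p = 0.031 whether they are 6/20 (30%) or 6/30 (20%).

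**How often chance alone reaches 5%.** This needs inputs that the protocol does not give. Assumed: bivariate normal changes in systolic and diastolic pressure, mean zero (no effect, no regression to the mean), correlation 0.6, and three pairs of SDs. The chance response rate is the probability of a fall of at least 20 systolic or at least 10 diastolic. Chance significance is then the binomial probability of at least 6 responders (exact) or at least 4 (uncorrected).

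| SD of change, systolic/diastolic (mmHg) | Chance response rate | n = 20: exact / uncorrected | n = 30: exact / uncorrected |
| --- | --- | --- | --- |
| 10/7 | 9% | 0.6% / 9% | 4% / 27% |
| 12/8 | 13% | 4% / 26% | 19% / 56% |
| 15/10 | 20% | 20% / 59% | 58% / 88% |

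**Which n applies.** The sample size section expects 67% to return at week 4, that is 30 × 0.67 = 20.1. A patient with no follow-up is either outside the full analysis set or has the baseline carried forward. In the second case the change is exactly zero and the patient cannot be a responder. About 20 patients can therefore respond by chance, and the n = 20 column fits the protocol's own expectation. The n = 30 column applies only if everyone is followed.

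**What an estimate would show.** Exact (Clopper-Pearson) 95% intervals: 6/20 = 30% (12% to 54%); 6/30 = 20% (8% to 39%). The interval separates two results to which the test gives the same p-value.

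**The case against.** The best defence is that little hangs on this. The response rate is one secondary outcome of an exploratory, uncontrolled study, and section 13.C disclaims any aim of establishing efficacy and says that percentages will be presented. The sentence in section 16 is general, and a statistical analysis plan could assign each variable to a test. Chance variation and regression to the mean affect every before-after comparison here, not only this one. All of that stands as a limit on the consequence. It does not rescue the test: section 16 states a rule for all categorical efficacy variables, and for this one the null is false by construction.

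The size is also open to challenge. The chance-significance figures rest on assumed SDs, and the largest need the uncorrected version with few discordant pairs, a setting in which many analysts would use the exact version. At n = 20 and SDs of 12/8 mmHg, the exact test is significant by chance in about 4% of studies, below the nominal 5%. So a reader might infer from the n = 30 column that the test will usually mislead; the protocol's own expected follow-up does not support that.

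A reader might also infer that McNemar is wrong for the pulse-wave parameters, since section 12.C records some of them as a value and a stage, for example "Pulse strength value and stage (Unit:gf". The documents do not establish this. Nowhere is stage classed as categorical, the number of stages is not given in the text (Attachment 1 is not shown), the outcome in section 13.B is an amount of change, and the Wilcoxon signed-rank test is already available in section 16.

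**Conclusion.** The test is wrong as written for the BP response rate. That conclusion, and the dependence of the p-value on the responder count alone, follow from the definition and need no assumption. The frequency of chance significance does depend on assumptions: with about 20 patients followed it is about 0.6%, 4% and 20% (exact) or 9%, 26% and 59% (uncorrected) for the three assumed SD pairs, before any regression to the mean.

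The consequence is confined to one secondary outcome. The primary analysis of change in mean sitting systolic pressure is unaffected. McNemar remains usable for BP below 140/90 mmHg, because patients on antihypertensive drugs may enter with a systolic pressure of 130 to 139 mmHg and so can be in either state at visit 1. Untreated patients enter at 140 mmHg or above, so their visit 1 state is fixed by the entry criterion.

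**What to change.** In section 16, exclude the BP response rate from the McNemar sentence. State that it will be reported as n/N with an exact (Clopper-Pearson) 95% confidence interval and without a test against baseline. Keep McNemar for yes/no states measured at both visits, such as BP below 140/90 mmHg, and replace the reference to normality with a usable rule for choosing the exact version, for instance the number of discordant pairs.

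The cost is a sentence or two. No visit, measurement or sample size changes. The sponsor gives up a p-value that had no useful meaning and gains an estimate with its precision, which is what planning the later randomised trial needs.

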- (Visit) Patients who take herbal medicine prescribed by Kyung Hee Bi, Che, Dam Korean Medicine Clinic are instructed to make f/u visits every 4 weeks for monitoring of AEs and clinical progress. In case of AEs, additional visits may be necessary.

1. Standard protocol tests

- The Standard management protocol at Kyung Hee Bi, Che, Dam Korean Medicine Clinic involves performing 3D BP waveform test and blood tests on patients taking herbal medicines every four weeks. In the present study, only patients taking modified SMS were enrolled. However, additional tests may be performed in cases of AEs.

1. Study intervention: administration of modified SMS per standard protocol

In the present study, we modified the traditional SMS formula used for CVD (ginseng, Ophiopogon japonicus, and Schisandra chinensis) based on clinical experience, classic texts, and experiment findings. We removed ginseng and added Platycodon grandiflorus and Pueraria lobata as well as Dioscorea opposita and Coix lacrymajobi to stimulate digestive functions. The formula consisting of **Pueraria lobata (5.33g), Platycodon grandiflorus (5.33g), Ophiopogon japonicus (5.33g), Dioscorea opposita (2.67g), Coix lacrymajobi (2.67g), and Schisandra chinensis (2.67g) (total 24g; unit g/day)** is referred to as saengmaeksangagambang (modified SMS). This is one of the unique empirical prescriptions used at Kyung Hee Bi, Che, Dam Korean Medicine Clinic. Although in actual practice at Kyung Hee Bi, Che, Dam Korean Medicine Clinic, **certain ingredients may be removed, doses may be adjusted, or other interventions such as acupuncture, may be added depending on the symptoms and disease being treated, such cases were excluded from the analysis in this study.**

- Patients take a 60-mL 70% alcohol-soaked decoction of the modified SMS formula prepared by Kyung Hee Bi, Che, Dam Korean Medicine Clinic twice daily before meals or between meals
- Dispensing of medicine on Visit 1, Visit 2: [number of days until next scheduled visit date (standard 28 days, maximum 35 days) + 3 days]* 2 packs. A standard of 62 packs, up to 76 packs, are packaged in a box or pack, labeled with the patient’s information.
- Participants will return unused medicine at the subsequent visit.
- Returned unused medications will be stored separately for each patient in a box/pack.
- At completion of trial, returned medicines will be disposed of following the facility’s medication disposal procedures.

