- Dose per pack: modified SMS: each pack contains 60 mL containing Pueraria lobata (5.33g), Platycodon grandiflorus (5.33g), Ophiopogon japonicus (5.33g), Dioscorea opposita (2.67g), Coix lacrymajobi (2.67g), and Schisandra chinensis (2.67g) (total 24g; unit g/day).
- Dosage: oral; 2 packs a day
- Treatment period: 8 weeks (56 days) (f/u every 4 weeks)
- Permitted concomitant treatments: Given the observational nature of this study, we will not limit any concomitant treatments and medications while undergoing the SMS regimen, and concomitant treatments will be documented.
  * Use/non-use of antihypertensive drugs will be documented.
  * If antihypertensive drugs are being used, patients are informed to notify the investigator upon changes in the dose and dosage of the drug.
  * Patients are informed to maintain their normal lifestyle, including exercise and diet.
- The dose and dosage of modified SMS used in this trial are identical to those used in actual practice at Kyung Hee Bi, Che, Dam Korean Medicine Clinic.

|  | | |
| --- | --- | --- |
| [figure not shown] | [figure not shown] | [figure not shown] |
| Cold extraction | Vacuum concentration | Concentrate |

Figure 5. Preparation facilities at Kyung Hee Bi, Che, Dam Korean Medicine Clinic and appearance of concentrates

1. Additional interventions, visits, and tests required for study participation per the purpose

The Standard management protocol at Kyung Hee Bi, Che, Dam Korean Medicine Clinic involves performing 3D BP waveform test and blood tests on patients taking herbal medicines every four weeks. In the present study, only patients taking modified SMS were enrolled. **Thus, there are no additional interventions required for participation in this study**

**In case of an adverse event, f/u is needed until the adverse event is resolved. In such cases, additional visits may be necessary.**

In case of an adverse event, additional tests, such as kidney function test, liver function test, and complete blood count, may be performed.

1. Control group, randomization, blinding

This is a single-group study without a control group, so randomization and blinding are not applicable.

1. Summary of study timeline (anticipated duration, place, staff in charge, study procedure)

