Even after voluntarily consenting to participate, participants may withdraw their consent at any time without any disadvantages. If a participant wishes to withdraw their consent or meets the criteria for study discontinuation, their personal information and relevant data will be excluded from the analysis and will be discarded immediately.

1. Risks and benefits for study participants
2. Potential risks

The study lacks a control group, and only routine intervention and tests are involved; thus, there is no added risk from study participation.

During routine treatment, modified SMS has little risk for side effects or tolerance, but gastrointestinal symptoms (indigestion, heartburn) and autonomic nervous system symptoms (palpitations) may occur.

Since no additional interventions or tests are involved, there will be no cases of injuries caused by participation in the study. However, issues arising from routine medical care can be compensated according to the clinic’s malpractice liability insurance policy.

1. Potential benefits

Since the treatment protocol for modified SMS at Kyung Hee Bi, Che, Dam Korean Medicine Clinic is followed, there is no direct benefit to participants from participating in the study.

However, by participating in the study, participants contribute to gathering information on the effectiveness of modified SMS in improving HTN and observing its progress, which can aid in the future development of Korean Medicine-based treatments for HTN.

1. Risk/benefits analysis

Considering the potential risks and potential benefits, there is a low risk of side effects and no additional benefits to treatment. However, there are also no additional risks posed by study participation. Thus, the study is deemed to pose minimal risk to the participants.

1. Compensation for study participation

The compensation for the study participants (e.g., transportation) is 50,000 KRW for each visit (1, 2, 3) for a total of 150,000 KRW. Visit 4 is a telephone f/u, so there is no compensation.

Participants’ bank account numbers will be additionally collected for payment of the compensation.

1. Measures to protect participants’ safety and personal information
2. Information collected for routine medical care and patient management

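### Section 17.C excludes and destroys the data of anyone who meets a discontinuation criterion, which contradicts the protocol's own FAS, Safety Set, LOCF rule, adverse event reporting and retention periods

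*Protocol*

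**What the plan says.** Section 17.C (Withdrawal of consent) has two triggers joined by an or: the participant wishes to withdraw consent, or the participant "meets the criteria for study discontinuation, their personal information and relevant data will be excluded from the analysis and will be discarded immediately". It makes no exception for safety data or for measurements already taken.

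The criteria in Section 17.A are broad. They include "Occurrence of SAE related to the herbal medicine or AE making continuation in the study difficult", "Lost to f/u during study period", "Participant’s violation of study plan" and a change of prescription. They also include requests to stop, eligibility violations and never taking a dose.

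Other sections assume that these participants' data remain:

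- **Section 16, FAS.** Citing the ITT principle, "FAS includes participants who have received the herbal medicine preparation at least once" and have at least one measurement of the primary outcome.
- **Section 16, Safety Set.** At least one dose and at least one safety follow-up.
- **Section 16, missing data.** Missing FAS values are filled by LOCF for efficacy.
- **Section 14, Evaluation of safety parameters.** All AEs in the study period are evaluated, and "The rate of AE, rate of AE that led to discontinuation, and rate of SAE are reported".
- **Table 2 footnote.** Case-conclusion data are collected when visits are completed or when the participant is discontinued.
- **Section 20, retention and disposal.** Study data are shredded three years after completion, and data sent to the sponsor through Mytrial are kept for ten years.

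The Method section is also divided. The standard protocol excludes those receiving other KM treatments. The intervention text says of changed ingredients, adjusted doses or added acupuncture that "such cases were excluded from the analysis in this study". The same text, under permitted concomitant treatments, says "we will not limit any concomitant treatments and medications while undergoing the SMS regimen".

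**The concern.** A participant who takes the product, has a baseline MSSBP and a safety follow-up, and then leaves because of an AE belongs to both analysis sets under Section 16. Under Section 17.C the same participant belongs to neither, and the record no longer exists. The protocol gives no order of precedence.

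The study's stated purpose is to explore safety and blood pressure lowering as preparation for a randomised trial. The 17.C rule removes the participants who matter most for tolerability. With a single arm, no comparison group would reveal the selection. Destruction cannot be undone, so a later analysis plan could not restore the sets that Section 16 defines.

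**Working it through.** **1. The protocol's own figure.** The sample size section wants data from 20 participants at 33% dropout: 20 / (1 − 0.33) = 29.85, rounded up to 30. This reproduces the stated 30, which is not in dispute.

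**2. Records affected.** 30 × 0.33 = 9.9, so about 10 lost. 30 × 0.67 = 20.1, so about 20 analysed under 17.C. Under Section 16 the FAS could hold up to 30, if the baseline MSSBP counts as the one required measurement. The 33% comes from the usual week-4 return rate of 67%, so it is an expectation and not a bound.

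**3. Rule against rule, for a treated participant who leaves.**

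| Item | Sections 14, 16, 20 and Table 2 | Section 17.C |
| --- | --- | --- |
| Efficacy | In FAS; gaps filled by LOCF | Excluded |
| Safety | In Safety Set after one safety follow-up | Excluded |
| AE leading to leaving | Counted and reported | No record to count |
| Case-conclusion data | Collected | Discarded immediately |
| Retention | Three or ten years | None |

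**4. Safety illustration.** Assumed: 30 treated, all with a safety follow-up; 10 leave, k of them because of an AE; 3 of the 20 who stay have an AE. Here discontinuation means leaving the study.

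| k | AE-discontinuation rate, Section 16 | Same, 17.C | Any-AE rate, Section 16 | Same, 17.C |
| --- | --- | --- | --- | --- |
| 1 | 1/30 = 3.3% | 0/20 | 4/30 = 13.3% | 3/20 = 15% |
| 3 | 3/30 = 10.0% | 0/20 | 6/30 = 20.0% | 3/20 = 15% |
| 5 | 5/30 = 16.7% | 0/20 | 8/30 = 26.7% | 3/20 = 15% |

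The 17.C columns do not move however many participants leave because of an AE. The any-AE rate can shift in either direction, because the denominator shrinks too.

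**5. Efficacy illustration.** Assumed: the 20 who stay have a mean MSSBP change of −10 mmHg, and the 10 who leave have a carried-forward mean change of d. The FAS mean is (20 × −10 + 10 × d) / 30.

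- d = 0: −200/30 = −6.7 mmHg
- d = −5: −250/30 = −8.3 mmHg
- d = −10: −300/30 = −10.0 mmHg

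Under 17.C the result is −10.0 mmHg in every case. The two rules agree only when those who leave have the same mean change as those who stay.

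**The case against.** **The text is softer than it looks.** Section 17.A says that participants may be discontinued, and 17.C stands under a heading about consent. Neither point resolves the conflict. The sentence acts on meeting a criterion, and it names discontinuation separately from withdrawal. If 17.A is discretionary, the investigator's discretion would decide who is analysed.

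**The study is exploratory and already plans on 20 with data.** This stands in part. The protocol disclaims an efficacy determination, and 30 enrolled is compatible with about 20 analysed. So the safety conflict carries more weight than the efficacy one. It does not reconcile two opposite rules on who is analysed.

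**Stronger readings are tempting, but the documents do not support them:**

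- *LOCF has nothing left to do.* It would no longer serve participants who leave, but it could still fill an isolated gap, such as a missing questionnaire in someone retained.
- *The AE-discontinuation rate must be zero.* That holds only if discontinuation means leaving the study. Section 14 also uses the word for stopping the regimen, with observation until the event resolves. A participant who stops but stays in the study could still be counted.
- *Every exclusion depends on response.* Eligibility violation and never being dosed do not. Loss to follow-up and plan violation need not.
- *The 25% termination rule would be counted on destroyed data.* AEs are documented as they arise and SAEs are reported promptly to the IRB, so a running count is possible.
- *The blood pressure effect is overstated by a known percentage.* Any such figure needs an assumed link between response and leaving. Take a true mean change of −6 mmHg, SD 12 and 33% leaving on a logistic model. The mean in those retained is −8.2 if the log-odds of leaving rise by 0.05 per mmHg of worse response, −6.0 with no link, and −3.8 if the link is reversed. The documents supply none of these inputs.

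**Conclusion.** The contradiction is real, and nothing else in the protocol resolves it. Followed as written, 17.C would remove about 10 of 30 records at the protocol's own dropout expectation. AEs that led participants to leave the study would disappear from the safety rates. The primary result would be close to a completer analysis.

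The count of about 10 assumes that those who drop out meet a 17.A criterion, which loss to follow-up alone would satisfy. The fall from 10% to 0 of about 20 rests on the assumed 3 AE-related departures among 30 with safety follow-up. The size and direction of the MSSBP bias depend on how leaving relates to response and cannot be derived from the documents. The point must be settled before any record is discarded.

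**What to change.** 1. In Section 17.C, limit exclusion and deletion to participants who withdraw consent and ask for erasure.
2. State there that data collected up to discontinuation for any other reason are kept, and are analysed in the FAS and Safety Set as Section 16 defines them.
3. State in Section 14 whether the rate of AEs leading to discontinuation refers to leaving the study or to stopping the regimen.
4. Reconcile the three statements in the Method section (the standard protocol exclusion, the exclusion from analysis in the intervention text, and the unrestricted concomitant treatment) on whether participants with changed prescriptions or other KM treatment are excluded or kept. More than one answer is defensible, but the protocol must give one.

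The cost is protocol wording and a matching line in the consent form. No extra participants, visits or tests are needed.
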